## Methods for measurement of endpoints (variables) for clinical safety

Two of the secondary endpoints are used for clinical safety;

1. Adverse events will continuously be registered during the study. The participants can fill out any AE in a web based digital diary and also contact the research midwife when needed. AEs will be registered in the CRF. AEs will be analyzed as proportion of women with AE and compared across study arma. For more details, see section 9.
2. Possible toxic effects on the vaginal cells after CHG treatment will be analyzed in vaginal biopsies described under 8.1.2. The analysis will focus on injuries of the epithelial lining and increase of inflammatory and immunological markers (antimicrobial peptides, cytokines, kemokins, CIDAMP). The biopsies will be taken at inclusion and at 3 months’ follow-up, when the prophylactic phase of the study is completed. Biopsies from participants allocated to FLZ will serve as controls.

# Handling of Adverse Events

## Definitions

### Adverse Event (AE)

Adverse Event (AE): Any untoward medical occurrence in a clinical investigation subject administered a medicinal product and, which does not necessarily have a causal relationship with the treatment, can be an unfavorable and unintended sign (including an abnormal laboratory discovery), symptom or disease temporally associated with the use of the medicinal (investigational) product, whether or not related to the medicinal (investigational) product.

### Adverse Reaction (AR)

In the pre-approval clinical experience with a new medicinal product or new use of a medicinal product, and particularly as the therapeutic dose(s) may not be established, all noxious and unintended reactions to the medicinal product related to any dose should be considered an adverse reaction (AR). The phrase “reaction” to a medicinal product means that the causal relationship between the medical product and an adverse event is at least a reasonable possibility, that is the relationship cannot be ruled out.

### Serious Adverse Event (SAE)

Serious adverse event (SAE): Any untoward medical occurrence that at any dose:

- results in death
- is life-threatening
- requires inpatient hospitalization or prolongation of existing hospitalization
- results in persistent or significant disability or incapacity
- results in a congenital anomaly/malformation

Medical and scientific assessment will be made to determine if an event is “serious” and whether it would prompt reporting in other situations, for example important medical events that may not be directly life-threatening or result in death or hospitalization but may compromise the study subject or may require intervention to prevent one of the other results set forth in the definitions above. These should also normally be considered as SAEs.

### Suspected Unexpected Serious Adverse Reaction (SUSAR)

SUSAR: A reaction/event that is unexpected, serious, and suspected to be caused by the treatment, i.e. adverse events that are not included in the Investigator’s Brochure (IB) or SPC.

## Assessment of Adverse Events

### Assessment of causal relationship

The investigator is responsible for determining whether there is a causal relationship between the AE/SAE and use of the investigational product.

Those AEs which are suspected of having a relationship to the investigational product will be followed up until the subject has recovered or is well taken care of and on their way to good recovery (see also section 9.4, Follow-up of Adverse Events).

All AE will be categorized either as likely related, possibly related, or not related, in accordance with the definitions below:

**Likely related**: Clinical event, including abnormal results from laboratory analyses, occurring within a reasonable time after administration of the intervention/investigational product. It is unlikely that the event can be attributed to underlying disease or other medications, but is most likely caused by the investigational product and its emergence is reasonable in relationship with use of the investigational product.

**Possibly related**: Clinical event, including abnormal results from laboratory analyses, occurring within a reasonable time after administration of the intervention/investigational product. The event could be explained by the investigational product and its emergence is reasonable in relationship with use of the investigational product, but there is insufficient information to determine the relationship. The event could be explained by an underlying disease or other medications.

**Not related**: Clinical event, including abnormal results from laboratory analyses, that is not reasonably related to the use of the intervention/investigational product. The event is unlikely related to the intervention/investigational product and can be explained by other medications or underlying disease.

### Assessment of intensity

Each adverse event shall be classified by an investigator as mild, moderate or severe.

**Mild:** The adverse event is relatively tolerable and transient in nature but does not affect the subject’s normal life.

**Moderate**: The adverse event causes deterioration of function but does not affect health. The event can be sufficiently unpleasant and interferes with normal activities but does not completely obstruct them.

**Severe**: The adverse event causes deterioration of function or work ability or poses a health risk to the subject.

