## Overall study design

The study is a 6 months clinical Phase II trial to compare if 1% chlorhexidine gluconate vaginal cream (Hibitane®) is at least as effective and safe as fluconazole (reference treatment) for culture-verified recurrent vulvovaginal candidiasis. The study is a randomized open non-inferiority trial with parallel treatment groups. The trial is not possible to blind for neither participants nor investigators due to the differences between study treatments. There is low risk of bias since the primary outcome variable is objective (negative vaginal culture for *Candida albicans*).

The rational for the study is to find an alternative treatment to fluconazole for RVVC with high tolerability and without cytotoxic effect on epithelial cells and negative impact on the vaginal microbes.

The participants will be randomization to;

- Investigational medication with Hibitane® vaginal cream 8 ml every night for a week and then prophylactic treatment with 8 ml/week for another 11 weeks

or

- Reference treatment with Fluconazole® 150 mg (oral capsule) every 3 days for the first 3 doses, then prophylactic treatment with 150 mg/week for another 11 weeks

Please see section 7 for more details on randomization and study treatments.

Figure 1 Study design

| **Visit** | **1** | **2** | **3** | **4** | **5** |
| --- | --- | --- | --- | --- | --- |
|  |  | CHG | Chlorhexidine gluconate  vaginal application  8 ml/w, 11 w | |  |
|  |  | 8 ml/day,1 w  R |  |  | N=30 |
|  |  |  | Fluconazole  oral capsules  150 mg/w, 11 w | |  |
|  |  | FLZ  150 mg/day,1w |  |  | N=30 |
| **Week:** | **-1** | **0** | **1** | **12** | **24** |
|  | Screening | Inclusion/  Baseline  Randomization | Follow-up | Follow-up | Follow-up and end of treatment |

##

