## Reporting and registration of Adverse Events

At each study visit, adverse events (AE) are continuously registered, starting from start of treatment with the investigational products, up to and including 12 weeks after the subject has ended their treatment with the investigational products. All AE that occur during the study and which are observed by the investigator/study midwife or reported by the subject will be registered in the CRF regardless of whether they are related to the investigational product or not. Assessment of causal relationship, severity, and whether the AE is considered to be an SAE or not will be done by the investigator directly in the *CRF*. The subjects can also report AEs in the digital weekly diary or via communication with the investigator/study midwife. At minimum, for each AE/SAE, a description of the event is recorded (diagnosis/symptom if diagnosis is missing), start and stop dates, causal relationship, severity, if the AE is considered to be an SAE or not, measures and outcome. These data will also be reported in the participant’s medical record.

All reported new symptoms in both study groups will be evaluated as a possible AE.

All AE shall be registered in the CRF from start of treatment to 12 weeks after end of prophylactic treatment *as above (section 9.3, Reporting and registration of Adverse Events)*.

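### The adverse event intensity grades in 9.2.2 are neither exclusive nor exhaustive: functional loss without a health effect fits both moderate and severe, and a tolerable but lasting event fits no grade

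*Protocol*

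**What the plan says.** Section 9.2.2 of the protocol (Assessment of intensity) sets a mandatory three-grade scale: "Each adverse event shall be classified by an investigator as mild, moderate or severe". The grades are defined as follows.

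- **Mild:** "The adverse event is relatively tolerable and transient in nature", with the further condition that the subject's normal life is not affected.
- **Moderate:** "The adverse event causes deterioration of function but does not affect health". A second sentence adds: "The event can be sufficiently unpleasant and interferes with normal activities but does not completely obstruct them", which limits this grade from above.
- **Severe:** "The adverse event causes deterioration of function or work ability or poses a health risk to the subject".

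Section 9.3 makes severity one of the minimum items recorded for each event and says who assigns it: "Assessment of causal relationship, severity, and whether the AE is considered to be an SAE or not will be done by the investigator directly", the entry being made on the case report form. The Overall study design section states that the assessor knows the arm: "The trial is not possible to blind for neither participants nor investigators due to the differences between study treatments".

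The adverse event endpoint (Secondary endpoint section, 8.1.2 and 8.2) is the proportion of women with adverse events, compared between arms. Events are also to be described and summarised for each arm; intensity is not named there.

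**The concern.** A grading scale works only if each event has exactly one correct grade. Here the written rule gives some events two grades and others none, although a grade must still be entered. Where the rule does not decide, the grader does, and in this open trial the grader knows the allocation. The protocol defends the open design by pointing to an objective primary outcome, the culture result. That defence does not extend to intensity, which is a judgement.

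At stake is the descriptive picture of tolerability. High tolerability of the cream is part of the stated rationale, and the one adverse event that the protocol lists for the cream is irritation of skin and mucosa. The cream is applied nightly for a week and then weekly for 11 weeks, so tolerable but continuing irritation is a plausible event in that arm.

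**Working it through.** No figure in the plan bears on this point, so there is nothing to recompute. The check treats the three definitions in 9.2.2 as logical conditions and asks whether they exclude one another and whether together they cover every event.

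**Conditions read from 9.2.2**

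- T: relatively tolerable
- S: transient
- N: normal life not affected
- F: function deteriorates
- W: work ability deteriorates
- H: health affected or at risk

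**Grades in these terms**

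- Mild = T and S and N
- Moderate = F and not H
- Severe = F or W or H

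**Test 1, exclusivity.** Take an event with F true and H false. Moderate is met in full. Severe is also met, because F alone is sufficient. So every event that meets the first sentence of moderate also meets severe. The second sentence of moderate does not remove the overlap. It sets an upper limit for moderate (activities not completely obstructed), but severe has no matching lower limit: it names no degree of deterioration and does not mention obstruction. An event that partly limits function therefore still meets severe.

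**Test 2, exhaustiveness.** Take an event with T and N true and S, F, W and H all false: tolerable, no effect on normal life, function, work or health, but lasting.

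| Grade | Met? | Reason |
|---|---|---|
| Mild | No | not transient |
| Moderate | No | function does not deteriorate |
| Severe | No | none of the three alternatives is true |

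The event has no grade, yet 9.2.2 requires one.

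**Test 3, who resolves it.** Under 9.3 the investigator enters the grade, and the trial is open. In the overlap, either moderate or severe can be entered without a protocol deviation. In the gap, no entry agrees with the text.

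**Test 4, what uses the grade.**

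- Between-arm adverse event comparison: proportion of women with any event; intensity not used.
- Serious adverse event reporting (9.1.3, 9.2.3, 9.3.1): separate criteria; intensity not used.
- Early termination (End of Study section): serious adverse events or recruitment; intensity not used.
- Descriptive summaries of events by arm: intensity not named, but recorded for every event and so available for tabulation.

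**The case against.** The strongest reply is that the scale is ordered. Moderate is limited by having no effect on health and by not completely obstructing activities, so a sensible grader would place severe beyond those limits. This is a fair guess at the intent, but the severe definition does not say it, and a grader who follows the text may enter severe for a partly limiting event.

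A second reply is that 'relatively' may qualify both tolerable and transient, and that most graders would call a lasting but harmless event mild in either arm. That is likely in practice, but it is the grader who repairs the rule, not the protocol.

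A third reply concerns consequences, and it stands: no decision rule in the protocol is tied to the severe grade, and the open design is disclosed and unavoidable.

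Four stronger readings are tempting, and the documents do not support them.

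- A reader might infer that a severity-by-arm comparison is planned. The protocol promises a descriptive summary of adverse events for each arm and does not name intensity.
- A reader might infer that irritation returning after each weekly application falls in the gap. If it resolves between applications, it can be read as a series of transient episodes and graded mild. The gap holds only for irritation that continues.
- A reader might infer that the tolerability conclusion could not be checked. Section 9.3 requires a description, start and stop dates, causality, measures and outcome for each event, so events can be re-examined without the grade.
- A reader might infer a bias of known direction. Nothing in the documents shows that events would be graded differently by arm; the wording only leaves room for it.

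**Conclusion.** The defect is real and lies in the protocol's own wording: the grades overlap for functional loss without a health effect, and they leave a gap for tolerable, lasting events without other effects. Only events in those two regions depend on the grader's choice. How many there would be cannot be derived from the documents, so no size in percentage points is given.

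The point is minor. The primary endpoint, the sample size, the formal adverse event endpoint and serious adverse event reporting are unaffected; what is exposed is any descriptive summary of intensity. The conclusion rests on a literal reading of 9.2.2, with 'or' in the severe definition taken as making each condition sufficient. It is not a matter to leave to the statistical analysis plan. That plan can decide how grades are tabulated, but it cannot make grades consistent once they have been recorded under an ambiguous rule.

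**What to change.** Reword 9.2.2 and the matching CRF text so that the grades lie on one axis, the degree of interference with normal activities (work included):

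- **Mild:** no interference, with or without symptoms and whatever the duration. Start and stop dates under 9.3 already capture duration, and the phrase 'with or without symptoms' covers abnormal laboratory findings, which 9.1.1 counts as adverse events.
- **Moderate:** some interference with normal activities or work, with neither completely obstructed.
- **Severe:** normal activities or work completely obstructed.

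Leave the serious adverse event criteria in 9.1.3 as they are, and do not move the health-risk condition into 9.2.3. That section only assigns responsibility for judging seriousness, and a general health-risk test there could widen what must be reported within 24 hours under 9.3.1. If the health-risk condition stays in the severe grade, state that it takes precedence over the interference axis, so that each event still has exactly one grade.

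The cost is a few lines in 9.2.2 and in the CRF, best made before grading starts. Sample size, visits and treatment do not change.

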### Assessment of seriousness

The investigator is responsible for assessing the seriousness (serious or non-serious). If the incident is considered serious, this should be reported as a serious adverse event (SAE) by the investigator to the sponsor. See also section 9.3.1, Reporting of Serious Adverse Events (SAE).

## Reporting and registration of Adverse Events

At each study visit, adverse events (AE) are continuously registered, starting from start of treatment with the investigational products, up to and including 12 weeks after the subject has ended their treatment with the investigational products. All AE that occur during the study and which are observed by the investigator/study midwife or reported by the subject will be registered in the CRF regardless of whether they are related to the investigational product or not. Assessment of causal relationship, severity, and whether the AE is considered to be an SAE or not will be done by the investigator directly in the *CRF*. The subjects can also report AEs in the digital weekly diary or via communication with the investigator/study midwife. At minimum, for each AE/SAE, a description of the event is recorded (diagnosis/symptom if diagnosis is missing), start and stop dates, causal relationship, severity, if the AE is considered to be an SAE or not, measures and outcome. These data will also be reported in the participant’s medical record.

All reported new symptoms in both study groups will be evaluated as a possible AE.

All AE shall be registered in the CRF from start of treatment to 12 weeks after end of prophylactic treatment *as above (section 9.3, Reporting and registration of Adverse Events)*.

### Reporting of Serious Adverse Events (SAE)

Serious adverse events (SAE) are reported to the sponsor on a special SAE form within 24 hours of the investigator being informed of the SAE.

Follow-up information describing the outcome and handling of the SAE is reported as soon as this information is available. The original should be kept in the Investigator Site File.

### Reporting of Suspected Unexpected Serious Adverse Reactions (SUSAR)

Those SAE which are assessed by sponsor to be SUSAR are reported via a [CIOMS form](https://cioms.ch/wp-content/uploads/2017/05/cioms-form1.pdf) to the European Medicines Agency (EudraVigilance database) according to the specified time frames.

SUSAR that are fatal or life-threatening are reported as soon as possible and no later than 7 days after the incident has become known to the sponsor. Relevant follow-up information is sent thereafter within an additional 8 days. Other SUSAR are reported as soon as possible and no later than 15 days after they have come to the sponsor’s knowledge.

## Follow-up of Adverse Events

Subjects who have been affected by adverse events (AE/SAE) will be followed-up until the adverse event is resolved or stable. Measures taken in case of unacceptable adverse events could be dose adjustment, treatment interruption or withdrawal of from the study.

## Annual Safety Report (Development Safety Update Report, DSUR)

The sponsor will submit an annual safety report to the Swedish Medical Products Agency including a list of all SAE that have occurred as well as possibly SUSAR. A summary assessment of the safety situation for the subjects and a benefit/risk evaluation for the study will also be reported.

## Procedures in case of emergencies, overdose or pregnancy

The sponsor and investigator will immediately take the urgent safety measures to protect the subjects from immediate danger. If needed the study may temporarily be suspended and supplementary monitoring measures might be introduced. The sponsor will inform the Swedish Medical Products Agency and EPM as soon as possible about the urgent safety measures taken.

If a study subject becomes pregnant, this person will be followed up until the birth has taken place. If the fetus/child will have any congenital malformation, this will be reported as a serious adverse event or side effect (SAE).

Adequate contraceptive method is an inclusion criteria and pregnancy test will be checked twice; before start of active and prophylactic treatment.

## Reference Safety Information

SmPC for Fluconazol and Hibitane are attached to the application (attachment 05, 06) The most common expected AE for each study medication are listed in the protocol (7.1).

# Statistics

## Analysis population

The study is a RCT controlled non-inferior trial with 60 women randomly assigned to either vaginal chlorhexidine gluconate (N=30) or oral fluconazole (N=30). Baseline plus 3 follow-up visits (baseline/inclusion, 1 week, 3 months and 6 months) are planned.

## Statistical analyses

### Statistical methods

***Objective:*** The aim of this study is to analyze whether vaginal chlorhexidine gluconate (CHG) is at least as effective and safe as oral fluconazole (FLZ) as treatment and prophylaxis for recurrent vulvovaginal candidiasis.

***Study design:*** Randomized controlled non-inferior trial with 60 women randomly assigned to either vaginal chlorhexidine gluconate (N=30) or oral fluconazole (N=30). Baseline plus 3 follow-up visits (baseline/inclusion, 1 week, 3 months and 6 months) are planned.

***Primary outcome****:* Proportion of women with negative cultures for *Candida albicans* 1week post-treatment.

***Secondary outcomes****:*

- Negative cultures for *Candida albicans* at 3 months’ and 6 months’ follow-ups, after end of prophylactic treatment.
- Analysis of proportion of women with adverse events (AE). The AEs will also be reported in descriptive terms and summarized for each treatment arm.
- Proportion of women with symptom score > 2. Each symptom of typical discharge, itching, dryness of the skin/mucosa, burning and pain will generate 1 point of a composite index (range 0-5).
- Proportion of women with examination score >2. Each finding of redness skin/mucosa, typical discharge, dry skin/mucosa, fissures skin/mucosa, visible candida hyphae in the microscope will generate 1 point of a composite index (range 0-5).
- Proportion of women with reduced vaginal lactobacilli content in vaginal smears measured by a semi-quantitative method as normal or reduced quantity.
- Proportion of women with relapse of *Candida albicans* infection between end of treatment and end of prophylactic treatment (1week post treatment to 3 months’ follow-up) and between 3- and 6 months’ follow-up after end of prophylactic treatment.
- Proportion of women with possible toxic effect on the vaginal epithelium, defined as disruption and/or inflammation of the epithelial lining, analyzed from vaginal biopsies before and after treatment and prophylaxis.
- Further analysis of mucosa inflammatory mechanism and biofilm formation during and after treatment and prophylaxis, analyzed from vaginal biopsies. The methods for these *in vitro* exploratory analyses are not yet decided on.

